### Statistical Analysis

#### Neuropsychological and clinical outcomes

There are no interim analyses planned unless requested for safety reasons by the DMEC. All estimates of efficacy will be based on a modified intention to treat (ITT) analysis including patients who have received at least one ECT treatment (given that this is a study of the effect of ketamine on ECT). The main statistical inference for both neuropsychological and efficacy outcomes will be made after 4 ECT sessions. In addition, the two treatment groups will be compared at the end of acute ECT treatment and 1 and 4 months later. Analysis methods are specified in a detailed Statistical Analysis Plan approved by the DMEC and TSC (available on request). Briefly, for neuropsychological data cross-sectional analysis of covariance (ANCOVA) models (allowing for stratifying variables, age, sex, baseline degree of treatment resistance, electrode placement [bilateral or unilateral] and baseline values of the outcome being studied) will be used to evaluate the effects of treatment allocation. The sensitivity of the findings to missing data will be assessed with inverse probability weighting adjustments. All analyses will involve the use of robust standard errors and associated confidence intervals (allowing for non-normality and constraints in the ranges of some of the cognitive outcomes). Efficacy data will be analysed using a random effects (random intercepts) ANCOVA model with time (in weeks) as a quantitative explanatory variable. The baseline variables will be the same as those for neuropsychological data. An interaction term between time and treatment allocation will also be included to assess the treatment effect.

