Ketamine is a dissociative anaesthetic, analgesic and psychotomimetic which inhibits NMDA receptors but also stimulates glutamate release and potentiates activity at non-NMDA receptors such as AMPA receptors [25]. Recent studies have shown a rapid antidepressant effect after a single dose of intravenous ketamine alone or as an adjunct to antidepressants in both unipolar and bipolar depression [26]. Repeated administration maintains improvement but relapse occurs rapidly on stopping treatment [27]. Side effects of ketamine treatment include acute anxiety, increased mood instability, vomiting, and vasovagal episodes, dissociation, dry mouth, tachycardia and increased blood pressure [27], though more severe cardiovascular side effects are associated with higher ketamine doses (0.8–1.0 mg/kg) [26].

Given acutely ketamine can cause cognitive impairment [28], particularly in manipulating information in working memory and encoding into episodic memory. However, preliminary human data from retrospective/non-randomised studies suggested that ketamine anaesthesia improves reorientation [29, 30] and word recall [31] after ECT, and also may result in more rapid clinical response [32]. Subsequent small randomised controlled trials (RCTs) have produced mixed results with studies suggesting impaired reorientation [33, 34] and improved [35] or unchanged [33] Mini Mental State Examination (MMSE) scores after ketamine. A further study found that ketamine augmentation produced no reduction in cognitive impairment after ultra-brief right unilateral stimulation on a range of tests [36]; however this technique is associated with minimal cognitive impairment compared with standard bilateral ECT which limits interpretation. Two recent meta-analyses looking at efficacy, and including the same 4 placebo-controlled RCTs in which ketamine has been combined with ECT, have reached different conclusions. When continuous measures were pooled a moderate to large advantage for ketamine was reported early in the ECT treatment course [26], but no benefit was found when end-of-treatment response and remission were meta-analysed [37]. The latter meta-analysis also reported higher rates of confusion/disorientation/prolonged delirium with ketamine. At present the small heterogeneous studies of ketamine augmentation of ECT emphasise the need for further larger scale trials.

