### Aims and Hypotheses

The primary aim of the Ketamine-ECT study is to investigate the effect of adjunctive ketamine on cognitive dysfunction caused by ECT using an RCT design with the hypothesis that ketamine, compared with saline treatment, given together with standard anaesthesia will reduce ECT-induced cognitive impairment. Secondary aims are to 1) investigate the efficacy, tolerability and acceptability of adjunctive ketamine (we hypothesise that ketamine treatment will lead to a more rapid improvement in depressive symptoms with fewer ECT treatments needed to achieve remission) and 2) to identify whether ketamine modifies ECT’s effect on frontal cortical function using functional near infrared spectroscopy (fNIRS) during performance of cognitive tasks.

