### Intervention

ECT and anaesthetic treatment protocols will be determined by the local ECT services but is required to be consistent with requirements given in the Royal College of Psychiatrists’ ECT handbook [46]; ECT being given twice a week. The anaesthetic induction agent of choice is propofol, with thiopental permissible as an alternative. For safety reasons etomidate cannot be used to avoid the potential for an interaction with ketamine excessively elevating blood pressure. Oral psychotropic medication continued by the patient’s treating clinical team will remain unchanged where possible for at least the first 4 ECT treatments, and ideally until end of ECT. The goal of ECT is to treat patients to remission (Montgomery-Åsberg Depression Rating Scale, MADRS ≤10) in accordance with NICE guidelines [4]. The final decision to end ECT will rest with the treating clinical team in consultation with the patient and the local ECT treatment team. Following recruitment, and before their first ECT treatment, patients will be randomised in a 1:1 ratio to receive ketamine 0.5 mg/kg or saline as a slow bolus before the anaesthetic induction agent. Randomisation will be by permuted block randomisation, stratified by NHS Trust, carried out by the Manchester Academic Health Science Centre Clinical Trials Unit (http://www.mahsc-ctu.co.uk/). Randomisation will occur by telephone and allocation communicated securely to each Trust Pharmacy which will securely over-package the study drug to conceal allocation. On the day of each treatment the anaesthetist will open the package and prepare the injection away from the ECT team and patient to maintain their blinding. Patients will receive the same allocated study medication throughout their course of ECT.

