#### Clinical efficacy measures

The primary efficacy measure will be change in MADRS score [48] from baseline with secondary outcomes listed in Table 1.

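### Efficacy is to be inferred after 4 ECT sessions, but the term named to assess it is a linear slope difference, which is a different quantity and can mislead

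*Protocol article*

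**What the plan says.** All of this is in the protocol article.

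- Neuropsychological and clinical outcomes, time point: "The main statistical inference for both neuropsychological and efficacy outcomes will be made after 4 ECT sessions".
- Same section, efficacy model: a "random effects (random intercepts) ANCOVA model with time (in weeks) as a quantitative explanatory variable". The baseline variables are those used for cognition, so the baseline value of the outcome is a covariate.
- Same section, term for treatment: "An interaction term between time and treatment allocation will also be included to assess the treatment effect".
- Same section, further comparisons: "the two treatment groups will be compared at the end of acute ECT treatment and 1 and 4 months later".
- Clinical efficacy measures: "The primary efficacy measure will be change in MADRS score" from baseline.
- Aims and Hypotheses: the team expects that "ketamine treatment will lead to a more rapid improvement in depressive symptoms with fewer ECT treatments needed to achieve remission".

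Cognition, in the same paragraph, gets a cross-sectional ANCOVA at each time point. The paragraph is a summary and refers to a separate SAP for detail.

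**The concern.** Two sentences in one paragraph point to different treatment effects for MADRS. The first is a difference in points at one moment, after the fourth treatment. The second is a difference in weekly rate of change, averaged along a straight line over whatever visits are in the model. They agree only if the gap between arms grows in proportion to time.

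There is reason to doubt that shape. One meta-analysis cited in the Background found that "a moderate to large advantage for ketamine was reported early in the ECT treatment course", while another of the same trials found no benefit at end of treatment. If an early gain later narrows, the arms converge after the first visit and the fitted slope difference favours saline. If the gain is complete by the first post-baseline visit and then holds, the slope difference is near zero when baseline is only a covariate. MADRS change is the lead efficacy measure, so a real early benefit could be reported as no effect or as slower improvement.

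**Working it through.** **The plan's own figure.** The revised power statement (80% at ES 0.57 with 100 patients, 0.58 with 95) reproduces: 80.6% with 50 per arm and 79.9% with 48 v 47 (two-sample t, two-sided 0.05). It is for HVLT-R. No power is stated for the MADRS interaction.

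**Inputs from the article.** 95 patients assessed, 1:1 (48 v 47); treatment frequency "ECT being given twice a week", so 4 ECT is nominally 4/2 = week 2; later comparisons at end of ECT and 1 and 4 months after it.

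**Assumptions not in the article.** End of ECT at week 5, hence follow-up near weeks 9 and 22; MADRS SD 10; within-patient correlation 0.5; complete data. D is ketamine minus saline, so negative favours ketamine.

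**Formulae.** With random intercepts and complete data, the expected interaction is the least-squares slope of D on t:

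- slope = Σ D(t − t̄) / Σ(t − t̄)²
- SE = √[SD²(1 − ρ)/Σ(t − t̄)² × (1/48 + 1/47)]
- implied week-2 contrast = mean D + slope × (2 − t̄)

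**Visits at weeks 2, 5, 9, 22, baseline as covariate only.** t̄ = 38/4 = 9.5. Σ(t − t̄)² = 56.25 + 20.25 + 0.25 + 156.25 = 233. SE = √(50/233 × 0.0421) = 0.095.

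| True D at the four visits | Slope per week | Significant, wrong direction | Implied week-2 contrast (true −5) |
|---|---|---|---|
| −5, 0, 0, 0 | 37.5/233 = +0.161 | 39% | −1.25 − 1.21 = −2.46 |
| −5, −2.5, −1, 0 | 49.25/233 = +0.211 | 60% | −2.125 − 1.585 = −3.71 |
| −5 throughout | 0 | 2.5% (5% rejection in all) | −5.00 |

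A direct comparison after 4 ECT for the same −5 points (d = 0.5) has 67% power unadjusted. It has 80% if baseline correlates 0.5 with outcome (d = 0.5/√0.75 = 0.58).

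**Sensitivity of the two fading patterns.**

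- Correlation 0.3: 30% and 47% wrong-direction significance. Correlation 0.7: 59% and 82%.
- Week-0 MADRS also kept as an outcome row: slopes +0.092 and +0.108 (SE 0.083), 20% and 26% in the wrong direction. The constant benefit is then detected with 32% power.

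**Sensitivity to the visit set.** These figures come from simulation (1,000 trials each, Monte Carlo error about 3 points). The true week-2 difference is −5.8, or 0.58 SD. The fading benefit is gone by week 5.

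| Visits in the model (weeks) | Fading: slope per week | Fading: wrong direction | Sustained: benefit detected |
|---|---|---|---|
| 2, 5, 9, 22 | +0.19 | 53% | 3% |
| 0, 2, 5, 9, 22 | +0.11 | 26% | 43% |
| 1 to 5 weekly | +0.99 | 59% | 24% |
| 0 to 5 weekly | +0.15 | 7% | 88% |
| 1 and 2 only | −2.8 | none beyond chance | about 30% |

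For weekly visits 0 to 5, direct calculation of the reversal agrees: slope 2.4/17.5 = +0.137, SE 0.347, giving about 6%. A direct comparison at week 2 keeps 79–83% power in every scenario.

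**The case against.** Four points can be made for the plan.

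1. A reader might infer that the model cannot estimate the effect after 4 ECT. That is not so. Treatment plus time-by-treatment terms give a week-2 contrast as a linear combination. It is exact if the difference is linear in time, if data stop at 4 ECT, or for a constant effect over weeks 2 to 22. What stands is that it is biased otherwise, and that the article names the interaction rather than this combination. Week 2 is also only nominal, since the Discussion notes that treatments are often missed.

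2. The size of the harm depends on visits the article does not list. It says arms are compared at the later time points, not that those visits enter the slope model. The week-22 visit alone supplies 156.25 of the 233 in the slope denominator. This stands: the 39–60% range is illustrative. Restricting to acute visits helps less than it may seem, because the low reversal figure needs week 0 as an outcome row.

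3. A reader might infer that the trial itself expects an early-only benefit. The Background reports two meta-analyses that disagree and calls the trials small and heterogeneous; the fading pattern is plausible, not predicted.

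4. A slope is a legitimate measure of speed of improvement, which is the stated secondary aim. This stands for a slope confined to the acute phase, so the interaction need not be banned.

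The unseen SAP may settle the visits and the contrast, and their absence from a summary is no fault. The mismatch between the two sentences, however, is in what the article does state.

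**Conclusion.** The point holds as a mismatch between the declared time of inference and the term declared to assess treatment. The interaction is not the MADRS difference after 4 ECT, and the week-2 contrast derived from the same model is unbiased only under restrictive conditions. If follow-up visits enter, the named test can give a null or reversed answer for a real early benefit. If data stop at 4 ECT the sign is right, but the slope has low power.

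The direction of the problem follows from the form of the model. Its magnitude rests on the assumed visit times, SD, correlation and shape of benefit, so confidence in any single percentage is moderate.

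It would go too far to conclude that the trial's main result is at risk. HVLT-R is analysed by cross-sectional ANCOVA and is untouched. Severity: should-fix, for a secondary outcome.

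**What to change.** Before unblinding, define the main efficacy effect as the baseline-adjusted mean MADRS difference at the assessment after the fourth ECT. Either of two analyses would deliver it:

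- the cross-sectional ANCOVA already planned for cognition, with the same covariates; or
- a repeated-measures model with visit as a categorical factor and treatment-by-visit terms.

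Report end of ECT and 1 and 4 months as secondary contrasts. Note that the end-of-ECT assessment is timed by the patient's response, whichever model is used.

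A slope restricted to the acute phase may be kept as a supplementary measure of speed of improvement. State which visits enter it and whether baseline is an outcome row or only a covariate, since the table of visit sets shows how much both matter.

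The cost is a change of analysis wording and a few more model parameters. No new data are needed.

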#### Mechanistic outcomes

fNIRS data will be preprocessed with HOMER2 (http://www.nmr.mgh.harvard.edu/PMI/resources/homer2/home.htm) converting them into HbO and HbR concentration changes after noise and motion artefact correction [55]. Primary analysis will be the region of interest (ROI) covering the key frontal cortical area and consist of the anterior optical channels. Channels will be discarded for very low optical intensity or high motion artefact according to standard protocols. Stimulus blocks will be averaged and the maximum haemodynamic changes determined for both HbO and HbR concentration in a time window based on the expected peak latency of the haemodynamic response. Repeated measures analysis of variance will be performed to compare patients and healthy controls and the effect of ECT and treatment allocation in patients, assigning 0 values to the missing channels within the ROI.

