#### Mechanistic measures

Bilateral dorsolateral and ventrolateral prefrontal cortex response to computerised tasks of verbal fluency (for category) and working memory (N-Back) will be measured using fNIRS, a portable brain imaging technique that can be used at the bedside or in a person’s home. This uses the differential light absorption properties of oxyhaemoglobin (HbO) and deoxyhaemoglobin (HbR) for near infrared light when it passes through the scalp, skull and superficial layers of the cortex from a light source placed on the scalp. The change in the light absorption spectra are measured with detectors placed nearby also on the scalp. The technique is analogous to functional magnetic resonance imaging (MRI) using blood oxygen level dependent changes, although it measures both HbO and HbR. It is possible to use fNIRS as a measure of functional changes in cortical blood flow secondary to neuronal activation [49].

In addition, a spatially resolved spectroscopy technique will be used, employing a modification of the diffusion equation of light transport, to provide an absolute measure of tissue oxygenation (the tissue oxygenation index). This index is the absolute percentage of total haemoglobin in the field of view which is oxygenated [50]. Its reliability and validity has yet to be established [51], however it does provide a potential absolute measure with which to assess cerebral tissue metabolism across groups and within subjects [52].

Two purpose built optical tomography systems (Biomedical Optics Research Laboratory, Dept. of Medical Physics and Bioengineering, University College London) provide a 48 channel array for topographical coverage of bilateral dorsolateral and ventrolateral prefrontal cortices.

Originally it had been planned to undertake glutamate magnetic resonance spectroscopy and structural and functional MRI in a subgroup, but this had to be halted when it became clear that insufficient patients would be recruited to allow valid analysis.

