#### Revised Power calculations

Following initial slow recruitment, the revised recruitment target was adjusted to 100 patients with 95 reaching the primary outcome measure point and the primary outcome was changed to the HVLT-R alone. This sample size provides 80 % power to detect an ES of 0.57 (ITT) and 0.58 (completer), two-sided *p* = 0.05. The target for recruitment to the mechanistic studies was decreased to a sample size of 20 patients (10 per treatment arm) and 50 controls. This has only a 21 % power to detect an ES of 0.6 with a two-sided *p* = 0.05 between the two treatment arms (10 per arm). Comparing 20 patients and 50 controls will give an ability to detect an ES of 0.6 between groups with 60 % power and two-sided *p* = 0.05, and a 70 % power to detect the same size of effect of ECT itself with a two-side *p* = 0.05.

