From the outset, recruitment to the study was anticipated to be challenging due to the narrow recruitment window between the decision to have ECT and the first treatment. In practice recruitment was further reduced by two additional factors. First, the number of patients receiving ECT has been decreasing so that the need to ensure a large enough pool from which to recruit has meant involving a large number of Trusts and ECT suites, each with their own procedural and governance requirements. Additionally, during set-up and the study itself, three ECT suites have closed due to NHS Trust reorganisations, requiring the identification of new sites. The delayed initiation of these new sites reduced capacity and available time to reach full recruitment. Second, the decrease in ECT prescribing has been combined with a trend to treat, on average, more severely ill patients, a higher proportion of whom than expected are ineligible for the study due to detention under the Mental Health Act or lack of capacity to consent. This has restricted our rate of recruitment, nevertheless, the revised recruitment target will still provide power to identify a clinically important effect size on a key cognitive measure, anterograde verbal memory measured by the HVLT-R.

With regard to the mechanistic studies, recruitment has been especially difficult because the clinical sites are more geographically scattered than originally planned, severely limiting the numbers of patients sufficiently close to the two imaging centres for MR imaging. It has raised practical difficulties in transporting the optical imaging equipment for the fNIRS assessments and in being able to do the testing before the first ECT session. In addition the severity of illness of the patients has meant that many are reluctant to undergo additional testing above the neuropsychological and efficacy assessments. This has meant having to discontinue the MR imaging and to severely curtail the recruitment numbers for fNIRS. Nevertheless we will be able to assess the feasibility and usefulness of fNIRS in this population in assessing depression and measuring and predicting the effects of ECT treatment, although the power to detect effects of ketamine augmentation will be very low.

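### The ketamine–saline fNIRS comparison treats the pre-ECT scan as an outcome in a repeated measures ANOVA instead of adjusting for it, giving away some precision at 10 patients per arm

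*Protocol article*

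**What the plan says.** The protocol article, Statistical Analysis, Mechanistic outcomes, assigns one method to three questions: "Repeated measures analysis of variance will be performed to compare patients and healthy controls and the effect of ECT and treatment allocation in patients". It names no baseline covariate for the allocation comparison.

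A scan before treatment is intended. Among the practical difficulties, the Discussion lists that of "in being able to do the testing before the first ECT session".

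Revised Power calculations gives the size: "The target for recruitment to the mechanistic studies was decreased to a sample size of 20 patients (10 per treatment arm) and 50 controls". For ketamine against saline it adds: "This has only a 21 % power to detect an ES of 0.6", at two-sided 0.05. The Discussion concedes that power for ketamine effects will be very low.

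Under Neuropsychological and clinical outcomes, the cognitive comparison of the same allocation uses ANCOVA, with the baseline value of each outcome among the covariates.

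**The concern.** Aims and Hypotheses asks, as a secondary aim, whether ketamine modifies the effect of ECT on frontal cortical function. The randomised arms answer that question, and a pre-randomised-treatment measurement of the same response is planned. Such a measurement can serve as a covariate, which removes the part of the follow-up variation that it predicts and corrects chance imbalance between small groups. Or it can serve as a first outcome, which in effect subtracts it with a fixed coefficient of 1. The second choice adds noise whenever the correlation between scans is not high. Repeated measures ANOVA makes the second choice, in the smallest comparison in the trial, while the article makes the first choice for cognition and does not explain the difference. What is at stake is precision. Under randomisation neither analysis is biased.

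**Working it through.** **Inputs.** From Revised Power calculations: 10 patients per arm, effect size 0.6, two-sided 0.05, stated power 21%. From Mechanistic outcomes: repeated measures ANOVA with no covariate named. Assumed, because the article does not give them: two scans per patient; equal variance at both scans; the effect of 0.6 expressed in SD units of a single scan and present only at follow-up; and a correlation *r* between scans, shown over a range.

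**Step 1: the stated power.** A two-sample t-test with 10 per arm has noncentrality 0.6/√(2/10) = 1.342 on 18 df and power 24.6% (26.8% by the normal approximation). A simulated Mann–Whitney test gives 21.6% (exact) or 21.4% (asymptotic), which matches the stated 21%. So the figure can be reproduced, but as a rank test on a single measurement and not as the planned ANOVA. That is a separate matter; the steps below do not use the 21%.

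**Step 2: what the ANOVA tests.** With two scans, the allocation-by-time F equals the square of the t statistic on change scores. A check on simulated data gave F = 7.6366 and t² = 7.6366, both with 18 residual df.

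**Step 3: variances of the treatment contrast**, with unit SD and 2/n = 0.2:

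- Change score: 0.2 × 2(1 − r).
- ANCOVA in large samples: 0.2 × (1 − r²), so the ratio to the change score is (1 + r)/2.
- ANCOVA at 10 per arm: chance baseline imbalance multiplies this by 1 + 1/16 (18 within-group df, minus 2), so the ratio is (1 + r)/2 × 17/16.

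**Step 4: numbers.** Powers are simulated (200,000 replicates; 18 df for change, 17 df for ANCOVA).

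| r (assumed) | Variance, change | Variance, ANCOVA | Ratio | Power, change | Power, ANCOVA |
|---|---|---|---|---|---|
| 0 | 0.400 | 0.213 | 0.53 | 14.6% | 23.5% |
| 0.3 | 0.280 | 0.193 | 0.69 | 19.0% | 25.3% |
| 0.5 | 0.200 | 0.159 | 0.80 | 24.6% | 29.6% |
| 0.7 | 0.120 | 0.108 | 0.90 | 37.4% | 40.7% |
| 0.8 | 0.080 | 0.077 | 0.96 | 51.9% | 53.8% |
| 0.9 | 0.040 | 0.040 | 1.01 | 80.9% | 80.4% |

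The simulated variance ratios agree with the formula: 0.53, 0.69, 0.80, 0.90, 0.96 and 1.01. The formula breaks even at (1 + r)/2 = 16/17, that is r = 15/17 ≈ 0.88.

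**Step 5: against ignoring the baseline.** A comparison of follow-up scans alone has variance 0.2 and power of about 24.5%. Below r = 0.5 the change-score test does worse than that (19.0% at r = 0.3).

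**The case against.** The strongest objection is that the article does not fix the model tightly enough to call it a change-score test. The visit schedule is in a figure that is not available, there are two tasks, two hemispheres and two haemoglobin measures that could be repeated factors, and the article refers to a detailed SAP. This stands in part: exact equivalence is conditional on two scans. With more scans, repeated measures ANOVA still treats baseline as an outcome. A SAP that specified ANCOVA would contradict the article's named method.

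It is also fair that the allocation-by-time test is valid and addresses the aim directly. The point is one of efficiency, not bias.

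Several stronger readings are tempting and are not supported:

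- A reader might infer that ANCOVA is never worse and is worth 54%, 33% or 18% more patients at r = 0.3, 0.5 and 0.7. Those figures invert the large-sample ratio (1 + r)/2. At 10 per arm the ratios 0.69, 0.80 and 0.90 correspond to about 45%, 25% and 11%, and near r = 0.9 ANCOVA is marginally worse.
- A reader might infer that ANOVA loses patients without a second scan and that ANCOVA would not. Complete-case ANCOVA drops the same patients.
- A reader might infer confounding by device or centre, since the article describes "Two purpose built optical tomography systems". If a patient is scanned on the same system each time, an additive device offset cancels in within-patient change. Allocation is stratified by Trust, and controls are recruited at the same two centres as patients. A device term may properly be left to the SAP.
- A reader might infer that ketamine is tested by the allocation main effect, which averages in the pre-treatment scan and would have only about 11–12% power at r = 0.3 to 0.7. The article does not say that this is the test.

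**Conclusion.** The point holds as a modest loss of precision. Under the two-scan assumption, and for correlations between 0.3 and 0.7, the planned test has a variance that baseline adjustment would cut by about 31% to 10%, and it forgoes roughly 6 to 3 percentage points of power at an effect size of 0.6. The size rests on a correlation that the article does not give, and the gain disappears near 0.9.

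Only the randomised ketamine–saline fNIRS contrast is affected. The HVLT-R primary analysis is not, and repeated measures ANOVA is not at fault for the within-patient effect of ECT. In the range 0.3 to 0.7 the comparison stays well short of usual power under either method, as the article itself accepts, so a better analysis does not make it confirmatory. The change is still worth making, because it costs almost nothing where more recruitment is not feasible and brings the fNIRS analysis into line with the cognitive one.

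**What to change.** In Mechanistic outcomes, separate the questions now covered by one sentence:

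- *Ketamine versus saline:* regress the follow-up region-of-interest response on allocation, with the baseline region-of-interest response as covariate. Alternatively, fit a mixed model with the baseline means constrained equal across arms, which also keeps patients who have only one scan.
- *Effect of ECT:* keep the within-patient pre–post change.

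Name the coefficient that tests ketamine, and state the scan times to which it refers. The cost is a change of wording and about one degree of freedom (17 instead of 18 with two scans). No extra patients or scans are needed.
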